**Methods:**

Seventy-two patients with PD, at the Affiliated Hospital of Shandong University of Traditional Chinese Medicine, were recruited and randomly divided into a control (n=36) and experimental group (n=36). The intervention group received conventional medicine plus Zhan Zhuang Qigong exercises five times a week at 30 min each time, over an 8-week period. The long-term effects of Zhan Zhuang Qigong on PD was investigated after the intervention. Phyphox APP, CRST, CPET, UPDRS(II, III) were used to evaluate tremor, aerobic capacity, and motor function in groups.

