### Sample size

This study is designed as a randomised controlled trial. The main outcome is the mean relief of upper limb static tremor after treatment. A review of previous studies showed that aerobic exercise could reduce upper limb static tremor amplitude by approximately 60%. It is estimated that the average tremor amplitude of the control group is approximately 76±136 mm, and the intervention group is expected to be reduced by 50 mm after training. The test level α is set at 0.05 (bilateral), the degree of certainty 1-β is set at 0.80 and the control:intervention group ratio=1:1. A sample size of 63 was calculated using *http://powerandsamplesize.com*. However, considering an abscission rate of about 15%, 72 patients with PD will be included.

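### The sample size of 63 (72 after dropout) does not follow from the protocol's own inputs, which need about 117 per group; the stated 80% power for 50 mm is not supported

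*Protocol article*

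**What the plan says.** The Sample size section gives a full set of inputs for a two-group comparison of tremor amplitude. It assumes that "the average tremor amplitude of the control group is approximately 76±136 mm, and the intervention group is expected to be reduced by 50 mm". Alpha is 0.05 two-sided, "the degree of certainty 1-β is set at 0.80", and the groups are equal in size. The result is reported as "A sample size of 63 was calculated using" an online calculator, and then, "considering an abscission rate of about 15%, 72 patients with PD will be included".

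The Abstract (36 patients in each group) and Study design and setting (72 patients divided 1:1) show that 72 is the total for both arms. The Mobile exercise test data section plans an independent two-sample t-test between groups if the amplitudes are normal with equal variance, and Mann-Whitney and median tests if they are not normal.

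The article gives no SD for the intervention arm, no SD of change, no correlation between baseline and follow-up, and no distributional form for amplitude.

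**The concern.** A 50 mm difference against an SD of 136 mm is a standardised difference of 50/136 = 0.37. A two-group trial with about 31 evaluable patients per arm cannot normally detect so small a standardised effect with 80% power, so either the number or an input is wrong.

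The 80% power claim is the stated justification for enrolling 72 patients. If it is wrong, a non-significant result could be read as evidence that the intervention fails, when on the plan's own assumptions the trial would more often than not miss the effect it was planned around.

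**Working it through.** **Inputs (all from the Sample size section).** Difference 50 mm; SD 136 mm, applied to both arms because only one is given; two-sided alpha 0.05 (z = 1.96); power 0.80 (z = 0.8416); ratio 1:1. (1.96 + 0.8416)² = 7.849.

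**Attempt to reproduce 63.**

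n per group = 2 × 7.849 × 136² / 50² = 116.1, so **117 per group, 234 in total** (118 per group with the exact t distribution). The 63 is not reproduced. As a total it is 63/234 = 27% of what is needed.

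**Other readings, per group unless stated.**

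- One-sided test: 92 (93 by t).
- Difference of 60% of 76 mm = 45.6 mm, two-sided: 140.
- Intervention SD shrinking in proportion to its mean, 136 × 26/76 = 46.5 mm: 7.849 × (136² + 46.5²)/50² = 64.9, so 65, or 130 in total.
- No variance at all in the intervention arm: 7.849 × 136²/50² = 58.1, so 59, or 118 in total.
- A single-group test: 59 (61 by t). This is near 63 but is not the stated 1:1 comparison.
- Standardised difference of 0.5: 2 × 7.849/0.25 = 62.8, so 63. This matches numerically, but per group, and for an SD of about 100 mm instead of 136 mm.

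No two-group reading of the stated inputs gives 63 in total.

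**Power for 50 mm at a common SD of 136 mm.** Normal approximation: Φ(50/(136 × √(2/n)) − 1.96), where n is the number per arm.

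| Evaluable per arm | Normal approximation | Noncentral t |
|---|---|---|
| 30 | 0.296 | 0.288 |
| 31.5 (63 in total) | 0.308 | 0.301 |
| 36 (all 72) | 0.345 | 0.337 |
| 63 (if 63 were per group) | 0.541 | 0.535 |

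**Difference detectable at 80% power.** 2.8016 × 136 × √(2/n) = 98.4 mm (n = 30), 96.0 mm (n = 31.5) and 89.8 mm (n = 36). All exceed the assumed control mean of 76 mm, so none could occur as a reduction from that mean.

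**What would make 63 in total correct.** For 50 mm, the SD of the analysed quantity would have to be about 71 mm (50 × √(31.5/2)/2.8016 = 70.8). Starting from 136 mm, this needs a baseline correlation of about 0.86 for a change score (1 − (70.8/136)²/2) or 0.85 for baseline-adjusted analysis (√(1 − (70.8/136)²)). The article states no such value.

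**Dropout step (minor).** 63/(1 − 0.15) = 74.1, so 75, or 76 for equal arms. The stated 72 is close to 63 × 1.15 = 72.45. At 15% loss, 72 leaves 61.2 evaluable; it retains 63 only up to 1 − 63/72 = 12.5% loss.

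**The case against.** The strongest objection is that about 30% describes one model: a t-test on raw amplitude with the same SD in both arms. A non-negative amplitude with mean 76 and SD 136 must be strongly skewed, so the planned normality check would usually send the analysis to the rank tests. In simulations with the intervention arm scaled to a mean of 26 mm and 30 patients per arm, Mann-Whitney power was about 91–92% if amplitude is log-normal and about 34–35% if it is gamma. Both shapes are assumptions from outside the article. This stands. A reader might infer that the trial's actual power is 30%; the article does not support that, nor any other single figure for the rank-test branch.

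The main outcome is also described as relief of tremor after treatment, which could mean a change score with a smaller SD. That is possible, but the 136 mm is attached to the amplitude, and the correlation needed (about 0.86) is not stated.

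Two further inferences should be resisted. One is that 63 came from using a per-group number for a standardised difference of 0.5 as the total. The numbers coincide, but the article does not say so. The other is that a log-scale analysis shows 72 patients to be enough. That needs a distribution the article does not give and a 60% reduction between arms. The Sample size section attributes roughly 60% to aerobic exercise, while Study design and setting gives the control arm aerobic walking, so the figure cannot simply be carried over as the between-arm effect.

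The dropout shortfall is small beside the main error, and the article says only about 15%. The gap between 60% and 50/76 = 65.8% sets an approximate literature figure against a rounded one and carries no weight.

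**Conclusion.** The sample-size statement is wrong as written. On its own inputs the two-sample calculation needs 117 per group against 36 randomised per arm. Even with zero variance in the intervention arm it needs 59 per group. The mismatch of 63 with the stated inputs does not depend on any distributional argument, because it concerns the calculation that the article itself reports.

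The power figures (29–30% with about 61–63 evaluable, 34% with all 72) and the detectable difference of 90–98 mm are conditional on normal theory and a common SD of 136 mm for the analysed quantity. Power under the rank-test branch could be much higher or about the same, and cannot be fixed from the article. What can be said is that the 80% claim has no support in the inputs given for it.

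**What to change.** Rewrite the Sample size paragraph in one of two ways.

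- **Keep the stated inputs.** Remove the claim of 80% power for 50 mm at SD 136 mm. State that 72 randomised, about 61 evaluable at 15% loss, give about 29–30% power for 50 mm by a two-sample t-test, and a detectable difference of about 97–98 mm at 80% power. For reference, meeting 80% on these inputs would take 117/0.85 = 137.6, so 138 per group or 276 randomised.
- **State what was actually used.** If the calculation rested on a different SD, a change score with a given correlation, or a particular distribution with a rank test, report that input and its source, and show that it yields the number.

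In either case inflate for dropout by dividing by 1 − 0.15: 63 becomes 75, or 76 for equal arms. Do not substitute a log-scale claim of 80% unless the distribution of amplitude and the expected effect against a walking control are each justified.

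The cost is one paragraph and a protocol amendment, with no extra patients if the size stays at 72. The price is a less favourable power statement, or an assumption that must be declared and defended.

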### Randomisation and allocation concealment and blinding

This study is single-blinded. Because of the Qigong intervention, training personnel and subjects are not blinded, however testers, data collectors, data scientists and analysts are blinded. Implementation of training, evaluation and statistical analysis of the separation of the way, that is, the training personnel do not contact the test personnel. Before testing, the intervention and control groups were renamed as groups A and B, respectively. The test tester is only responsible for the test by number, and does not tell the group of the test subject. Data collection and processing personnel are separated; data collection personnel obtain group A or group B date based on the number and prove this information to the data statistician for statistical analysis. To ensure study objectivity, quality control personnel will identify groups after statistics are completed.

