### Study design and setting

The study will be conducted in the Affiliated Hospital of Shandong University of Traditional Chinese Medicine. We will include 72 patients with PD with obvious upper limb static tremor. Recruitment will begin on 1 June 2022 and run until 1 June 2023. Using the random number table method, 72 patients will be randomly divided into an intervention and control group in a 1:1 ratio. Basic patient information, including gender, age, disease course, education level, residence status and drug-use will be collected. Tremor and motor function tests will be performed at least 8 hours after patients stop taking medication.

The control group will be treated with conventional medicine and routine aerobics. According to the Chinese Guidelines for the Treatment of PD (fourth edition), walking will be selected as the aerobic exercise mode in this group,^27^ five times a week at 30 min each time for 8 weeks. A combined cardiopulmonary exercise test (CPET) (treadmill test) will be used to measure peak oxygen uptake (peakVO_2_) in patients with PD at baseline and after intervention, and also anaerobic threshold (AT) and maximum heart rate (HRmax). During training, patients exercise intensity will be controlled at moderate exercise intensity (HRmax (60%–80%) measured by CPET or 11–13 Rating of Perceived Exertion (RPE). Changes in peakVO_2_ and AT at baseline and after intervention will be evaluated for improvements in aerobic exercise capacity. Walking will be performed about 1 hour after patients take their medication, and the tremor symptoms were resolved or disappeared.

The intervention group will take conventional medicine combined with Zhan Zhuang Qigong. An experienced Qigong master will guide Zhan Zhuang exercise. Week 1 will comprise the learning phase, while weeks 2–8 will be the practice phases, to be performed five times a week at 30 min each time. Intensity HRmax (60%–80%) will be measured using a cardiopulmonary combined exercise test or RPE test grade 11–13. Patients will be issued a training instruction manual and a personal exercise calendar to record the number of weekly exercises and time of each exercise. Zhan Zhuang training will be about 1 hour after patients take their medication, and tremor symptoms were relieved or disappeared. One auxiliary staff member will oversee safety measures.

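### The protocol prints the A/B key and sends the A/B labels to data collectors and the statistician, so their masking fails against anyone who has read it

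*Protocol article*

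**What the plan says.** All the relevant text is in the protocol article, section 'Randomisation and allocation concealment and blinding'. Trainers and participants are not blinded. Of the others, the section says that "testers, data collectors, data scientists and analysts are blinded". It then describes the mechanism:

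- Coding, before testing: "the intervention and control groups were renamed as groups A and B, respectively".
- Testers: "The test tester is only responsible for the test by number, and does not tell the group of the test subject". Trainers are kept apart from them.
- Labels: "data collection personnel obtain group A or group B date based on the number and prove this information to the data statistician", where 'date' and 'prove' evidently stand for 'data' and 'provide'. Data collection and data processing staff are said to be separate.
- Unmasking: "quality control personnel will identify groups after statistics are completed".

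The article does not say that the code in use differs from the printed one, that it was drawn at random, or that it is withheld from the data staff.

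**The concern.** A coded group label masks its holder only while the key is withheld. Here the key, the list of people who receive the labels, and the claim that those people are blinded all stand in one paragraph. The closing step, in which quality control staff reveal the groups, presumes a secret that the paragraph has already disclosed.

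Participants and trainers know the allocation, so the masking of testers and of data staff is the protection that remains. Some room for judgement is left on the data side. The section 'Mobile exercise test data' names both a median test and a Mann-Whitney test for non-normal data. The section 'CPET test data' takes the anaerobic threshold from the point where carbon dioxide output visibly accelerates relative to oxygen uptake. Someone who knows which arm is which could, without intending to, let that knowledge influence the handling of records or the choice of analysis. A report that repeats the claim of blinded analysts would also claim a safeguard that the published procedure does not secure.

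**Working it through.** No figure in the plan bears on this point, so the check sets the statements side by side and adds a check of dates.

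**1. Does the text fix the code?** Yes. The sentence names intervention then control, and A then B, and ends in 'respectively'. Read literally, A is intervention and B is control.

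**2. Who receives a label?**

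| Role | Claimed blinded | Described as receiving A/B |
|---|---|---|
| Testers | yes | no; they work by number |
| Data collectors | yes | yes; they look it up by number |
| Analysts (the statistician) | yes | yes; passed on by the data collectors |
| Data scientists | yes | not stated, unless they are the same people as the statistician |

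Two of the four roles claimed as blinded are expressly given the label. For a third the text is silent, and the fourth works without it.

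**3. What does the unmasking step add?** A person who holds a label and has read the code already knows the arm. The step in which "quality control personnel will identify groups after statistics are completed" therefore reveals nothing to that person.

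**4. When did the key become public?** Inputs: the article is dated 11 July 2022; in 'Study design and setting', "Recruitment will begin on 1 June 2022 and run until 1 June 2023"; outcomes are collected at weeks 9 and 17 ('Statistical analysis' and its Table 1).

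- Earliest week-9 visit, at the end of 8 full weeks: 1 June 2022 + 56 days = 27 July 2022. Counting 9 full weeks gives 1 June 2022 + 63 days = 3 August 2022.
- Last week-17 visit for a participant starting on 1 June 2023: + 112 days = 21 September 2023 (16 full weeks), or + 119 days = 28 September 2023 (17 full weeks).
- The article date precedes the earliest post-baseline visit by 16 days (27 July) or 23 days (3 August), and the last visit by more than 14 months.

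On the stated dates, and if each participant starts training on entry, the key was public before the first post-baseline outcome and well before any final analysis. A later start for any participant only widens the gap.

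**The case against.** The strongest reply is that the labels were plainly meant to be masked, since the groups are to be identified only at the end. The English is loose throughout, so 'respectively' may be a careless description of a neutral recode. Custody of the key is also the kind of detail that an article leaves to the full protocol. Part of this stands: the absence of a custody procedure is not criticised here. But the pairing is printed, not omitted, and a fuller document cannot make a published key secret; only a different code can. If the wording is merely loose, it still contradicts the claim made in the same paragraph and needs correcting.

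Several stronger readings are tempting, and the document does not support them:

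- **That blinding of the data side does not exist.** The text shows that the mask is open to a reader of the protocol. It does not show that any data collector or analyst has read the code or used it.
- **That outcome assessment is unblinded.** Testers work by number, have no contact with trainers and are not described as receiving a label. The evaluator blinding stated in the Abstract and under 'Methods and analysis' is not refuted by this wording.
- **That the people who process the phone signal or read the anaerobic threshold know the arm.** Collection and processing staff are separate, and nothing says that the processors or readers get a label.
- **That arms are known from the first record.** The article does not say when collectors look up the label; it could be when files are assembled for the statistician.

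The scope for influence is also narrowed by stated rules: a Fourier transform for amplitude and frequency, a Shapiro-Wilk cut-off of 0.05 for the choice between parametric and non-parametric tests, and fixed averaging windows with a named V-slope method for the exercise test. This limits the harm without restoring the mask.

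**Conclusion.** The point holds in a limited form. The paragraph asserts a property, blinding of data collectors and analysts until the statistics are complete, and then describes a procedure that does not deliver it to anyone who has read the protocol. The exposure is confined to the staff described as receiving the labels, namely the data collectors and the statistician. It does not extend to the testers, and it is not shown to extend to signal processing or threshold reading.

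The size of any bias cannot be derived from the document, and none is asserted. The conclusion rests on reading 'respectively' literally and on the printed code being the one in use. It does not require that any member of staff actually knows the key. It should be corrected, because the remedy costs little and the claim of blinded analysis cannot be relied on without it.

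**What to change.** Deleting 'respectively' from an article already in print re-masks no one. The effective steps are:

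1. The holder of the randomisation list draws a new neutral label mapping at random. Letters other than A and B would avoid carrying over the published pairing. The mapping is not disclosed and stays sealed until the analysis is signed off.
2. Data collectors work by participant number only and receive no group label.
3. The masked labels are merged for the statistician only after the phone amplitudes and anaerobic threshold readings are final and the database is locked.
4. The blinding section is amended to describe this, without stating the mapping.

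The cost is a short task for the list holder and a small change to the data-handling workflow: a sealed key and a merge after lock. If the recode is not done, the claim that data collectors and analysts are blinded should be withdrawn and the trial reported as blinded at the level of the testers.

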## Assessment result

### Primary outcome

(1)Static tremor of the upper limbs

① Mobile phone movement exercise test

Phyphox APP^28^ is based on the Android system (V.1. 1. 9). It collects the static tremor date of the upper limb of patients with an obvious tremor, at a frequency of 100 Hz over 30 s.

Data collection on the static tremor: The patient relaxes, sits in a chair, places his/her hands on the armrest and holds the mobile phone with the screen up on the shaking side. At the same time, patients perform numerical subtraction calculations to distract their attention. The time from the beginning of the tremor is recorded over 30 s.

② The Clinical Tremor Rating Scale (CRST) A+B, CRST-A is used to evaluate the tremor at rest, postural and intentional; CRST-B assesses handwriting (dominant hand only), wide and narrow spiral drawing, straight lines and casting. For the dominant hand, the maximum subscore of hand tremor is 32 for CRST (A+B) and 28 for the non-dominant hand. The higher the score, the more severe the tremor.

(2)Aerobic capacity

Combined Cardiopulmonary Exercise Test (CPET)

The cardiovit CS-200 cardiopulmonary combined exercise test system (SCHILLER, Switzerland) is used for CPET. The treadmill test is performed, and the increasing rate set at 10 W/min. Based on standards from Harbor-UCLA Center Cardiopulmonary Exercise Laboratory, USA, the resting state lung function examination, including fast lung capacity, slow lung capacity, maximum minute ventilation capacity and diffusion function, should be completed first. Symptom limiting maximum CPET is then completed using continuous ramping regimen.^29–31^ CPET is divided into four stages, including 3 min of rest, 3 min warm-up (no treadmill power), then exercise at an increasing power rate of 10 W/min until symptom limiting maximum exercise, followed by more than 5 min of recovery.^32^ Continuous 12-lead ECG, non-invasive cuff blood pressure and oxygen saturation measurements are required during the CPET process. PeakVO_2_, AT, and HRmax are measured and recorded.

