PD tremor is influenced by attention and stress levels.^47^ Previous studies reported that tremors were intentionally attenuated when attention was focused on them, and that PD tremors were is amplified by stress.^48^ Wang^49^ using nuclear magnetic resonance to analyse tremor subtypes in patients with PD, observed that the brains of tremor subtypes in patients with a wide range of functional connection between the frontal lobe and cerebellum, and UPDRS score III movement and the cognitive function score also existed significant correlation, that movement function and cognitive function in patients with PD has a high degree of correlation. DA substitution therapy also alleviated some motor characteristics in PD, but the observed beneficial effects on cognitive function were small.^50^ Several studies^21 51 52^ reported that Zhan Zhuang enhanced the attention and cognitive ability of adolescents and the elderly. Yiyue Chen^53^ observed that Zhan Zhuang exercises increased P3 wave amplitude in frontal, central and top regions, with a shorter incubation period when compared with baseline. P3 wave amplitude reflected the allocation of neural electrical resources, and latency which was related to the speed of stimulus classification. These results suggest that station post affected neural electrical processing related to cognitive control, by changing neural electrical resource allocation and stimulus classification speeds, thereby affecting cognitive function. Therefore, the station post may indirectly improve tremor performance by enhancing cognitive ability in patients.

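### The phone tremor measure appears to be one 30 s recording per visit; averaging three would cut its variance modestly for a few extra minutes

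*Protocol article*

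**What the plan says.** Under Primary outcome, the protocol article describes the mobile phone test: the seated patient holds the phone on the shaking side with the hands on the armrest and does mental subtraction, while data are collected "at a frequency of 100 Hz over 30 s", timed from the onset of tremor. Table 1 ticks this test once each at baseline, week 9 and week 17. The section on mobile exercise test data converts the signal to amplitude and frequency by Fourier transform and compares groups with a two-sample t-test or, if the data are not normal, with median and Mann-Whitney tests. Repeats and averaging over recordings are not mentioned.

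Study design and setting requires tremor testing at least 8 hours off medication. The Discussion says that "PD tremor is influenced by attention and stress levels".

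The Sample size section uses this amplitude. It states that "the average tremor amplitude of the control group is approximately 76±136 mm" and that "the intervention group is expected to be reduced by 50 mm after training".

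**The concern.** If the visit value comes from one short sample, all within-visit fluctuation of a symptom that the article itself calls sensitive to attention and stress enters that value. This adds to the outcome variance. Repeating the recording at a visit that is already scheduled costs very little and removes part of it.

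The article is otherwise specific about acquisition. For the phone test it gives sampling rate, duration, posture and distraction task. For the cardiopulmonary test it gives the averaging windows (10 s at the anaerobic threshold, 30 s at peak). One would expect repeats of the tremor recording to be mentioned at the same level of detail if they were planned.

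What is at stake is precision, not bias. On the stated inputs the amplitude comparison has little precision to spare.

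**Working it through.** **Inputs from the Sample size section:** difference 50 mm; SD 136 mm; two-sided α 0.05; power 0.80; 1:1 allocation; 63 patients before dropout; 72 after about 15% dropout. Completers: 72 × 0.85 = 61.2, or 30.6 per arm.

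**The plan's own figure.** Two-mean formula: n per arm = 2 × [136 × (1.960 + 0.842) / 50]² = 2 × 58.07 = 116.1, so 117 per arm and 234 in total. The stated 63 is not reproduced. That is a separate matter; here it only sets the starting point.

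**Power with one recording.** Standard error = 136 × √(2/30.6) = 34.8 mm. 50/34.8 = 1.44, and Φ(1.44 − 1.96) ≈ 0.30. With all 36 per arm it is about 0.34.

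**Effect of averaging k recordings.** Let ICC be the share of single-recording variance that is stable within a visit. The document gives no value, so it is assumed. The variance ratio is v = ICC + (1 − ICC)/k, and the SD becomes 136 × √v, taking 136 mm as the SD of one recording. For k = 3:

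| ICC (assumed) | v | Variance reduction | SD (mm) | n per arm for 80% power | Power at 30.6 per arm |
|---|---|---|---|---|---|
| 0.60 | 0.733 | 27% | 116.5 | 86 | 38.9% |
| 0.70 | 0.800 | 20% | 121.6 | 93 | 36.2% |
| 0.80 | 0.867 | 13% | 126.6 | 101 | 33.9% |
| 0.90 | 0.933 | 7% | 131.4 | 109 | 31.9% |
| 0.95 | 0.967 | 3% | 133.7 | 113 | 30.9% |

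**Limit of the remedy.** 80% power at 30.6 per arm needs an SD of about 69.8 mm, that is (69.8/136)² = 0.26 of the present variance. Three recordings cannot go below 1/3 even at ICC = 0.

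**If the analysis were baseline-adjusted (not planned).** Let ρ be the correlation of true levels between visits, assumed to be 0.7–0.9.
- One recording: residual variance 1 − (ρ·ICC)².
- Mean of three: v × [1 − (ρ·ICC/v)²].
- ICC 0.9, ρ 0.7: 0.508/0.603 = 0.842, a 16% reduction.
- ICC 0.6, ρ 0.9: 0.336/0.708 = 0.474, a 53% reduction.

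**The case against.** **The article never says that only one recording is made.** Correct. A tick per visit in Table 1 is compatible with repeats, and a condensed article may leave the number of recordings to a test manual. A reader might infer that a single recording is an established fact. The text supports only that one recording is what it describes.

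**The conditions are already standardised.** This stands in part. Off-medication testing, the relaxed seated posture, the subtraction task and the start at tremor onset all reduce fluctuation. At 4–6 Hz, 30 s already covers about 120–180 cycles. These features make a high ICC plausible, which is why 0.95 is shown. They do not remove slower variation between one half-minute and the next.

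**An SD nearly twice the mean might be taken as evidence of a noisy measurement.** The documents do not support that. An SD above the mean of a non-negative quantity points to skew, and the spread may lie mainly between patients, which repeats cannot reduce. Back-to-back repeats also leave day-to-day variation untouched.

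**A reader might infer a much larger gain.** The 16–53% reduction above is equivalent to about 19–111% more patients. It needs a baseline-adjusted analysis, and the analysis sections name two-sample tests with no covariate. The Sample size section does call the outcome mean relief, which could mean a change score, but the article does not say that change is what will be compared.

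**The phone test is only one of several measures listed as primary.** True, but it is the one whose amplitude the trial was sized on.

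**Conclusion.** The point holds as an optional efficiency improvement, not as an error or contradiction. As described, the amplitude measure appears to rest on one 30 s recording per visit. If repeats are exchangeable, averaging them cannot raise the variance; only the size of the gain is uncertain.

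For the planned unadjusted comparison, three recordings lower the variance by 7–27% at an assumed ICC of 0.6–0.9, and by about 3% at 0.95. Power at about 31 completers per arm goes from about 30% to about 32–39%. These figures assume that 136 mm is the SD of a single recording and use a normal approximation. With amplitudes as skewed as the stated mean and SD suggest, they are a guide only.

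It would be wrong to infer that repeats rescue the sample size. The gap between the stated 63 and the 234 given by the document's own inputs remains, and it is the larger problem.

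**What to change.** State the number of recordings per visit and the averaging rule. Take three 30 s recordings at baseline, week 9 and week 17, with the same hand, posture and subtraction task and a short rest between them. Analyse the mean of the three amplitudes as the visit value. A log scale is a separate choice and is not needed for this purpose.

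The cost is two more 30 s recordings plus rests with the same phone and tester: a few minutes per visit, possibly more because recording starts at tremor onset and tremor may have to re-emerge each time. Slight fatigue, or practice on the subtraction task, is possible and should be similar in both arms. If repeats are already part of the test procedure, a sentence saying so settles the point.
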